### Sample size calculation

We will calculate the sample size required for this study based on previously collected data in Datong (another county in Qinghai), in which exclusive breastfeeding for 0–6 months children was only 29.2% (unpublished data in 2017). We expect to achieve a 20% increase in the exclusive breastfeeding rate by using the WeChat intervention. With a power of 80 and 5% significance level, we calculate that a sample size of 93 pregnant women respectively for intervention and control group will be sufficient for all the primary and secondary outcomes. To compensate for possible refusal and loss to follow-up, we will enroll 200 pregnant women for intervention and control group, respectively. To achieve this sample size, all eligible pregnant women in the 13 townships will be selected as participants over an estimated period of 15 days.

### Recruitment and randomization

Before the baseline survey, each township hospital will firstly provide a list of names of all women who are 14–36 weeks pregnant of their own township, which also includes information on gestational age, gravidity and parity. In addition, we will ask the township hospitals to highlight on the list pregnant women who are not at home all the year, do not receive antenatal care in township hospitals, or are unable to use a smartphone. Based on the inclusion and exclusion criteria, they will be asked to come to their own township hospitals. Those who meet the eligibility criteria will be given full information about the study. After signing the written informed consent and completing a basic demographic questionnaire, all the eligible participants will be randomized to either the WeChat intervention group or the control group at a 1:1 ratio.

An independent statistician who will not participate in recruitment or data collection will generate 400 random numbers using Microsoft Excel. She will use the median of the random numbers as a threshold. Random numbers lower or equal to the median will be allocated to the intervention group and random numbers higher than the median will be allocated to the control group. The random numbers and the allocated group will be printed on small cards, and kept in opaque, sealed envelopes. At the back of the random number card, the two-dimensional codes of the WeChat official account “Huzhu County Maternal and Child Health Family Planning Service Centre” will be printed. In addition, the two-dimensional code of “Assistant 1” will also be printed at the back of the random number card for intervention group and “Assistant 2” for control group. “Assistant 1” and “Assistant 2” will be used by study team members for future follow-up.

After an eligible pregnant woman agrees to participate and has signed the written consent form, a researcher will give the next envelope in sequence to her, and she will open the envelope to check the random number to determine the assigned group. All the pregnant women in both intervention group and control group will be asked to follow the WeChat account “Huzhu County Maternal and Child Health Family Planning Service Centre” on their smartphone through scanning the two-dimensional codes at the back of random number card. If the pregnant woman is assigned to the intervention group, the researcher will help her to subscribe to and register with the “ke Xue Wei Yang (Optimal feeding)” module in the official account, and make a brief introduction of the module. If the pregnant woman is assigned to the control group, the researcher will inform her about the study procedures, including the follow-up interviews. Both the intervention group and control group need to subscribe to the “Assistant” WeChat account for future follow-up. As pregnant women in the control group cannot register with the “ke Xue Wei Yang (Optimal feeding)” module, they cannot access to the information in the module, which avoids between group contaminations through direct sharing of messages sent via WeChat.

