## Discussion

This paper describes the study protocol for a randomized controlled trial of a WeChat breastfeeding promotion, which will aim to encourage mothers to exclusively breastfeed their children if they can in the first 6 months postpartum. To our knowledge, this will be the first randomized controlled trial of using WeChat to support mothers on breastfeeding in China.

In China, the exclusive breastfeeding rate is quite low. Moreover, national data showed it decreased by more than one percentage point annually between 2008 and 2013 [8]. It is urgent to explore effective ways to control this down trend, and research in this area is needed. Given the widespread use of WeChat and a large number of active users, WeChat can be an important health promotion tool in China. Therefore, our study will provide important insights in using a WeChat intervention to improve the exclusive breastfeeding rate in China.

Our study will examine the WeChat intervention’s effect on the exclusive breastfeeding rate and duration using a rigorous randomized controlled trial design, which will ensure balance among the confounding variables in each group and eliminate the bias caused by characteristics of the participants. We hypothesize that the intervention group will have a higher exclusive breastfeeding rate and longer exclusive breastfeeding duration than in the control group. Our WeChat intervention delivery is based on the local county WeChat official account, which makes the program sustainable as the county will be able to continue using the account.

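### Township, known for every woman, is used neither in the allocation list nor in the named analyses; the allocation is valid, and using township would be a cheap, optional gain in precision

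*Protocol article*

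**What the plan says.** Under Recruitment and randomization, an independent statistician "will generate 400 random numbers using Microsoft Excel". The rule is one threshold for the whole list: "She will use the median of the random numbers as a threshold", and "Random numbers lower or equal to the median will be allocated to the intervention group"; higher numbers go to control. The cards sit in opaque, sealed envelopes, and after consent "a researcher will give the next envelope in sequence to her". The stated aim is that participants are "randomized to either the WeChat intervention group or the control group at a 1:1 ratio".

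Recruitment is by site. Listed women are screened locally: "they will be asked to come to their own township hospitals". Under Sample size calculation the target is 200 per group, to be reached because "all eligible pregnant women in the 13 townships will be selected as participants over an estimated period of 15 days".

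Data management and analysis names chi-square tests, Kaplan-Meier curves with a log-rank test, Cox regression and logistic regression. Township appears in none of them. The Discussion credits the randomised design, "which will ensure balance among the confounding variables in each group and eliminate the bias caused by characteristics of the participants". It mentions township only as a possible route of contamination and as a limit on generalisability.

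**The concern.** Splitting 400 distinct numbers at their median is in effect one block of 400. It fixes the overall split at 200:200 once every envelope is used, but restricts nothing within a township. If feeding practice or routine care differs between townships, the arms can differ somewhat in township mix by chance. An analysis without township leaves that variation in the error of the comparison.

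What is at stake is precision, not bias. Township is known for every woman before randomisation, so using it costs little. The Discussion's wording is also stronger than any randomisation can support, since randomisation balances covariates on average and does not guarantee it in one trial.

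**Working it through.** **Inputs from the protocol article.** Control rate 29.2%; expected increase 20 points, so 49.2%; power 80%; two-sided 5%; 93 per group required and 200 per group enrolled; 13 townships; all randomised women kept in the analysis.

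**Assumptions.** The SD of township rates (10 to 15 percentage points) and, where used, about 31 women per township (400/13). Neither figure is in the article.

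**1. The plan's own figure.** With mean rate p = (0.292 + 0.492)/2 = 0.392:

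n = [1.96·√(2 × 0.392 × 0.608) + 0.842·√(0.292 × 0.708 + 0.492 × 0.508)]² / 0.20² = (1.353 + 0.569)² / 0.04 ≈ 92.4, so 93 per group. This reproduces the stated number and confirms that the increase is meant in absolute points. Power at 200 per group is 98.5%.

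**2. Standard error without township.** Outcome variance is 0.392 × 0.608 = 0.2383.

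SE = √(0.2383 × 2/200) = 0.0488, or about 4.9 points.

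**3. Share of variance held by township.**
- SD 0.10: 0.0100/0.2383 = 4.2%
- SD 0.15: 0.0225/0.2383 = 9.4%

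**4. Contribution of chance township imbalance to the arm difference.**
- SD 0.10: √(0.0100 × 2/200) = 1.0 point
- SD 0.15: √(0.0225 × 2/200) = 1.5 points (about 1.4 if the 13 townships are treated as a sample from a wider set, a factor of √(12/13))

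**5. Standard error with township accounted for.**
- SD 0.10: √[(0.2383 − 0.0100) × 2/200] = 4.78 points
- SD 0.15: √[(0.2383 − 0.0225) × 2/200] = 4.65 points

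So 4.9 falls to 4.6-4.8 points, a reduction of about 2 to 5%.

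**6. Splits within one township, for context.** The intervention count among 31 women is hypergeometric (400, 200, 31): SD = √(31 × 0.25 × 369/399) = 2.68, 95% range 10 to 21, with a 26% chance of a split of 60:40 or worse. These figures describe one township. Step 4 gives what they amount to for the overall comparison.

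**7. Enrolment below 400, for context.** At 300 women the intervention arm has a 95% range of 142 to 158. Power is 94.7% at 142/158. At 150/150, (0.200 − 0.1105)/0.0552 = 1.62 gives 94.8%. At 186 women, power is 79.7% at 83/103 against 80.3% at 93/93. Unequal arms cost almost nothing.

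**The case against.** The strongest reply is that nothing here is an error, and most of that reply stands. An independent statistician, sealed opaque envelopes and sequential use give unbiased allocation, with an expected 1:1 ratio at every enrolment up to 400. Randomising without site strata is a legitimate choice, and the chi-square test stays valid because its standard error already carries chance imbalance in prognostic factors. With 98.5% power at 200 per group, there is no power problem to solve.

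Three stronger readings are tempting, and the document does not support them.

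- *That 1:1 fails at any total other than 400.* Below 400 the ratio drifts slightly, at negligible cost (step 7). Above 400 no allocation is defined. However, the article sets 200 per group as the target, presents taking all eligible women as the means to reach it, and prepares 400 allocations. The absence of an explicit stop is a gap in wording.
- *That uneven splits within townships endanger the result.* A 60:40 split somewhere is very likely, but the quantity of interest is the overall arm difference. On it, township adds an SD of 1.0 to 1.5 points, against a standard error of 4.9 and a planned effect of 20.
- *That the Discussion promises balance by township or of group size.* It speaks of confounding variables in general. The phrase needs an edit; it does not show a fault in the scheme.

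It is also fair to say that covariate terms are often left to a fuller analysis plan, which is not at hand. Township is therefore proposed here as an addition, not reported as an omission.

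Lastly, blocking by township has a price. The woman opens her envelope with the researcher present, so recruiters see past assignments, and short blocks in a series of about 31 make later ones partly guessable. The single list largely avoids this.

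**Conclusion.** The allocation is sound and the planned tests are valid. What remains is a small, avoidable loss of precision: a known site variable is used neither in the allocation nor in the named analyses. Under an assumed between-township SD of 10 to 15 points, township holds 4 to 9% of outcome variance, and using it lowers the standard error from about 4.9 to 4.6-4.8 points. With a smaller true SD the gain shrinks towards nothing. The calculation is on the risk-difference scale at the planning rates with 200 women per arm; it does not depend on township sizes if the SD is taken over women.

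This is an optional, cheap improvement. Neither the single-township split probabilities nor the drift from 1:1 below 400 should be presented as a threat to the trial's conclusion.

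**What to change.** 1. **Data management and analysis (main change).** Add township as a stratum or model term: Mantel-Haenszel or logistic regression for the exclusive breastfeeding rates, and stratified log-rank and Cox for duration. Merge very small townships by a rule fixed in advance. Cost: one term in each model, and township recorded for each woman.

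2. **Recruitment and randomization (preferable, before recruitment).** Have the same independent statistician prepare a concealed envelope series for each township, or group of townships, in randomly permuted blocks of varying, undisclosed size, with spare envelopes. This also settles how one sequence is shared among 13 hospitals and what happens after envelope 400. Cost: a new list and up to 13 envelope sets. The downside is somewhat more predictable allocation within a township; larger blocks limit it. If this is adopted, change 1 should accompany it so that the analysis matches the allocation. If it is declined because of predictability, change 1 alone secures most of the gain.

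3. **Discussion.** Say that randomisation is expected to balance confounders on average, and drop the claims that balance is ensured and bias eliminated. Cost: one sentence.

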### Intervention

A WeChat official account will be used to deliver health education messages related to breastfeeding. The intervention is based on the existing WeChat official account “Huzhu County Maternal and Child Health Family Planning Service Centre” applied by Huzhu County Maternal and Child Health Family Planning Service Centre. The Huzhu County Maternal and Child Health Family Planning Service Centre and Capital Institute of Pediatrics jointly developed a special module “ke Xue Wei Yang (Optimal feeding)” for the WeChat official account with the technological support of a specialized information technology company (ZYZY (Beijing) Pioneer of Cultural Essence Co. Ltd.). All the participants in the intervention group will be asked to register with the module after completing the baseline survey. Before becoming members of the module, they will have to read the introduction of this study. They will be asked to register and provide information regarding their name, phone number, gestational age, expected date of delivery, village and county where they live. After they will be provided and can log in with a WeChat identification and password.

The official WeChat account includes the following four components: feeding lecture classroom, feeding knowledge competition, baby growth chart and online forum. Each component is described in detail (Fig. 2).

**Fig. 2 Fig2:**
[figure not shown]
The interface of the WeChat interventions. (**a**) Login interface, (**b**) Main interface, (**c**) Feeding lecture classroom, (**d**) Feeding competition, (**e**) Baby growth chart, (**f**) Online forum, (**g**) Rewards, (**h**) Rankings

The ***feeding lecture classroom*** is designed to provide key breastfeeding knowledge and relevant infant feeding advice. Participants can read new messages and review the message history of all content published in the official account. The education messages will be shown in the form of text, videos, and pictures.

All breastfeeding health education messages are developed based on the WHO breastfeeding recommendations, guidelines, and published literature [3–6, 13–16, 24–27]. There are four phases in the development of health education messages: 1) a breastfeeding information database was first developed according to the recommendations, guidelines, and published literatures, which will include all the related breastfeeding themes and the key themes of this database are summarized in Table 1; 2) a research group meeting was held to identify all the detailed messages that will be published in the feeding lecture classroom; 3) each message will be compiled by one research team member who will develop appropriate multimedia content using videos, pictures, or records to effectively convey the meaning of each message and each message will be revised with expert opinion and subsequently approved by all research team members; 4) another research team member will be responsible for publishing all the messages in the feeding lecture classroom in the official account “Huzhu County Maternal and Child Health Family Planning Service Centre” before baseline. All the pregnant women and mothers in the intervention group can log into the feeding lecture classroom to read and learn all those breastfeeding messages.

**Table 1 Tab1:** Key themes of breastfeeding promotion education

Category	Key themes
Core messages	➢ Importance and benefits of exclusive breastfeeding ➢ Early initiation breastfeeding ➢ Cues to start feeding and the signs of infant satisfaction ➢ Breastfeeding on demand ➢ Frequency of breastfeeding ➢ Breastfeeding positions and latching-on ➢ Benefits of breastfeeding ➢ Weaning time ➢ Normal milk supply ➢ Rooming-in
Breastfeeding problems encountered for both mother and child	➢ Return to work and breastfeeding ➢ Risks of formula supplements ➢ Specific guidance for women who had cesarean section delivery ➢ Determining adequate intake ➢ Common misunderstandings about breast feeding
Preparation	➢ Preparation for breastfeeding ➢ Preparation for starting solid foods at 6 months

In addition, we suppose that there are three key stages for mothers, late pregnancy (37 weeks or above), the first month postpartum and 4 months postpartum, during which breastfeeding information needs to be strengthened. Three sets of tailored messages will be sent to all pregnant women and mothers at these stages via their WeChat on Monday, Wednesday and Friday every week. Specifically, for the late pregnancy stage, information on getting ready for breastfeeding and key breastfeeding recommendations will be sent to pregnant women whose gestational weeks are 37 weeks or above. For the first month postpartum stage, the key breastfeeding recommendations and breastfeeding problems encountered for both mother and child will be sent to new mothers. For the 4 months postpartum stage, information on starting complementary feeding at 6 months to avoid introducing complementary food too early or too late will be sent to mothers whose children were 4 months old or above.

The ***feeding knowledge competition*** component aims to test how well mothers know the breastfeeding knowledge. Participants need to participate once in the third and fourth week of each month.

The ***baby growth chart*** component is developed based on the WHO growth chart standard. Mothers can enter data on weight and height of their children whenever they want to monitor their children’s growth. Once the data are reported, a feedback message on whether their children’s weight and height are between the 3rd and 97th percentiles will be provided to mothers immediately.

The ***online forum*** component is designed to provide a feedback activity between mothers and experts. Mothers can ask breastfeeding related questions on the forum and three experts from the Capital Institute of Pediatrics will give feedback answers through the WeChat platform. Once the feedback is send, mothers will receive a WeChat message which reminds them to review the feedback answers.

Additionally, there will be an “Express” function which will send system notification alert, including updated feeding messages, competition and questionnaires.

A **rewards component** will also be developed to stimulate mothers to participate in our study. During the intervention, mothers can receive scores as long as they participate in WeChat activities. Different types of activities will result in different scores (Table 2). We will rank the scores mothers receive every month, and the top 10 WeChat active mothers will be given rewards, such as toys, picture books, or children towels.

**Table 2 Tab2:** Scores received from activities

Activities	Scores (points)
Registration	20
Read and review the breastfeeding messages in the feeding lecture classroom	5 per message
Share learning experience	2 per message
Score the feeding messages	1 per message
Feeding knowledge competition	2 per time
Questionnaires	20 per time
Baby growth chart	2 per time

The “ke Xue Wei Yang (Optimal feeding)” module was pre-tested in Huzhu County in Aug 2018. Semi-structured interviews were conducted among 17 pregnant women in their second or third trimester and 16 mothers who had a child aged 0–6 months to learn their use experience of the platform to learn from their experience in using the platform. They generally accepted the platform, as they thought the information was easy to understand and useful. They also suggested that both videos and text&picture should be delivered to mothers, as some mothers like video, while some like text&pictures. The detailed description of the methods and results of the pre-test will be reported elsewhere (manuscript in preparation).

### Control group

Mothers in the control group will only receive the routine antenatal and postnatal health care services (as will the intervention group). Participating infants in both groups will receive routine physical checkups (1, 3, 6, 9 and 12 months) in their own village clinics during their first year [7]. Although participants in the control group will also follow the “Huzhu County Maternal and Child Health Family Planning Service Centre” WeChat official account, they cannot log in the “ke Xue Wei Yang (Optimal feeding)” module and get feeding information from the module.

### Outcome measurement

The primary outcome in this study will be the exclusive breastfeeding rate at month 1, month 3, and month 6 postpartum in both the intervention group and the control group. Secondary outcomes for both intervention group and control group will be as following: 1) the overall duration of any and exclusive breastfeeding across the first 6 months postpartum; 2) mothers’ knowledge on breastfeeding practices; 3) the proportion of early initiation of breastfeeding; 4) the timing of the introduction of solid food to infants.

Exclusive breastfeeding will be defined according to the WHO definition which says that the infant receives breast milk as the only source of food; no other liquids or solids are allowed with the exception of vitamin and mineral supplements or medication [28]. The duration of exclusive breastfeeding is defined as the time in weeks until mothers introduce food or drink except for breast milk (we will ask mothers in the follow-up survey “When did your child first eat or drink other food or liquid except for breast milk, including drinking water?” ).

Any breastfeeding will be defined as the infant receiving any breast milk along with other food or liquids, including formula. The duration of any breastfeeding is defined as the time in weeks until a mother stops breastfeeding completely (we will ask mothers in the follow-up survey “When did you completely stop breastfeeding to your child?”).

Early initiation of breastfeeding will be defined based on the WHO guideline as the infant being put to the mother’s breast within one hour of birth [28].

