**Methods:**

The study is designed as a randomized controlled trial in rural Qinghai Province, China. Women who are 14–36 weeks pregnant will be randomized to routine antenatal and postnatal care, or routine care plus the WeChat breastfeeding education. pregnant women with a severe disease and complications of pregnancy or HIV-1 will be excluded. Breastfeeding knowledge and promotion information will be delivered to the intervention group through a WeChat official account from 3 months pregnancy to 6 months postpartum. The outcome assessments are conducted at baseline through face-to-face interviews, and at one week, 1 month, 3 months and 6 months postpartum by telephone interviews. The primary outcome is difference in the exclusive breastfeeding rate at 1 month, 3 months, and 6 months postpartum between the intervention group and the control group. Secondary outcomes include the overall duration of any and exclusive breastfeeding across the first 6 months postpartum; mothers’ knowledge of breastfeeding; the proportion of early initiation of breastfeeding; and the timing of the introduction of solid food to infants. Intention-to-treat-analysis will be used. Survival analysis will be used to compare the overall duration of any and exclusive breastfeeding between groups.

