### Data management and analysis

One research staff member blinded to the treatment allocation will be in charge of database maintenance and management. Logic verification statements will be written in data acquisition software for the smartphone. Baseline data and follow-up data will be saved first on the smartphone, and then wirelessly uploaded into an Excel database via an internet server [29].

Statistical analyses will be performed by the research staff using SAS 9.2 software (SAS Institute, Cary, NC). Continuous variables will be presented as mean and deviation, while categorical variables as numbers and proportions. The homogeneity in baseline characteristics between the intervention group and control group will be estimated using t tests for continuous variables andχ^2^ test for categorical variables. In addition, theχ^2^ test will also be used to compare the differences of exclusive breastfeeding rate between two group at one week, 1 month, 3 months, and 6 months postpartum. Survival analysis will be used to compare the overall duration of any and exclusive breastfeeding between the groups. We will construct Kaplan-Meier survival curves to estimate the median exclusive breastfeeding times and use the log-rank test to compare the differences. We will also perform Cox proportional hazards regression to estimate hazard ratios for stopping exclusive breastfeeding or any breastfeeding.

The principle of intention-to-treat-analysis will be used. This means that participants who drop out or are lost to follow-up during the postpartum period will be considered to have stopped breastfeeding at the point of the last follow-up contact and all randomized participants will be included in the analysis. We will further calculate the odds ratios of any and exclusive breastfeeding at each follow-up time point using logistic regression. All statistical tests will be two-tailed and *P* < 0.05 will be considered significant.

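### Three unranked primary time points, each tested at unadjusted P<0.05 with no success rule: if any one month suffices, the false-positive rate is about 8 to 14%, not 5%

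*Protocol article*

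**What the plan says.** Outcome measurement defines the primary outcome at three visits: "The primary outcome in this study will be the exclusive breastfeeding rate at month 1, month 3, and month 6 postpartum". The abstract's Methods paragraph names the same three: "The primary outcome is difference in the exclusive breastfeeding rate at 1 month, 3 months, and 6 months postpartum".

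Data management and analysis uses the chi-square test to "compare the differences of exclusive breastfeeding rate between two group at one week, 1 month, 3 months, and 6 months postpartum". One week is tested as well, but it is not named as primary. The same section sets a single threshold for everything: "All statistical tests will be two-tailed", and P below 0.05 "will be considered significant".

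The sample size calculation rests on one comparison: "With a power of 80 and 5% significance level", using one control rate for the whole 0 to 6 month period and an expected rise of 20 points. The resulting 93 per arm is described as enough for every primary and secondary outcome; 200 per arm will be enrolled.

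No section names a lead month, a testing order, a split of alpha, a joint test over the visits, or an any-one or all-three rule. The hypothesis in the Discussion speaks of a higher rate without naming a month.

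**The concern.** Three tests can each carry the primary claim, each has the full 5%, and the rule that turns three P values into one conclusion is missing. As written, the investigators could report success on the primary outcome from whichever month is significant, and could choose that month after seeing the data. The stated 5% would then not be the error rate of the headline claim. The effect may well differ between months 1, 3 and 6, so a split result is realistic, and the plan gives no way to read one.

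The sample-size statement depends on the same missing rule. A number derived for one test at 5% cannot be called sufficient for all primary outcomes until it is known how the three tests combine.

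**Working it through.** **1. Reproduce the plan's figure.** Inputs from Sample size calculation: control rate "exclusive breastfeeding for 0–6 months children was only 29.2"%; intervention rate 29.2 + 20 = 49.2%; two-sided 5%; 80% power. With pooled variance under the null and no continuity correction,

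n = [z(1−α/2)·√(2p̄(1−p̄)) + z(0.80)·√(p1(1−p1)+p2(1−p2))]² / (p2−p1)²

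p̄ = 0.392, the two square roots are 0.6904 and 0.6758, and z = 1.960 and 0.842. This gives n = 92.3, so **93 per arm**, as stated. The figure is that of one test at the full 5%. (Reading 20% as a relative increase gives 1003 per arm, so the absolute reading is the one used.)

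**2. False-positive rate if any one month suffices.** With no true effect and independent tests: 1 − 0.95³ = **14.3%** two-sided, and 1 − 0.975³ = 7.3% in the intervention's favour.

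The visits are correlated. The protocol gives neither correlations nor rates per visit, so the rest is a range over assumptions, by simulation of three correlated normal statistics with cut-off 1.96.

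| Equal correlation (assumed) | Any of three, two-sided | Any of three, favouring intervention |
|---|---|---|
| 0 | 14.3% | 7.3% |
| 0.5 | 12.6% | 6.3% |
| 0.7 | 10.9% | 5.5% |
| 0.9 | 8.4% | 4.2% |

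If exclusive breastfeeding at a later visit implies it at every earlier one, the correlation between an early rate a and a later rate b is √[b(1−a)/(a(1−b))].

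| Rates at months 1/3/6 (assumed) | Two-sided | Favouring intervention |
|---|---|---|
| 60/35/10% | 12.7% | 6.4% |
| 80/60/29.2% | 12.5% | 6.2% |
| 60/45/29.2% | 11.2% | 5.6% |
| 50/40/29.2% | 10.3% | 5.1% |
| 29.2/25/20% | 9.1% | 4.5% |

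Every case examined exceeds the nominal 5% (two-sided) or 2.5% (one direction).

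**3. If all three must be significant.** The error is below 5% in every case above: 2.3% two-sided at correlation 0.9, and less at lower correlations. There is no inflation. Power suffers instead: even if each month had the planned 80.3% at 93 per arm, joint power would be lower than that unless the tests were perfectly correlated (0.803³ = 52% if independent).

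**4. Power if the error is controlled.** Same formula, 29.2% v 49.2%, at α = 0.05/3 = 0.0167 (z = 2.394), which is Holm's first and strictest step. Here n = 123.4, so **124 per arm** for 80% power.

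| Evaluable per arm | Power at 0.05 | Power at 0.0167 |
|---|---|---|
| 93 | 80.3% | 65.8% |
| 160 | 95.9% | 90.3% |
| 200 | 98.5% | 95.9% |

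The 160 illustrates a 20% loss; the protocol gives no expected loss.

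**The case against.** The strongest reply is that the inflation is conditional. A reader might infer that the trial's false-positive rate simply is 11 to 14%. The documents do not support that. It holds only if one significant month is enough, which the plan leaves open, and under an all-three rule the error stays below 5%. For the same reason it would be wrong to call the three visits co-primary, a term that strictly means all must succeed; multiple primary time points is the exact description. The 11% lower limit also depends on assumed rates per visit, and flatter profiles or higher correlation take it down to about 8 to 9%. Finally, the two-sided figure includes false results in favour of control, which nobody would report as success. All of this stands and is reflected in the size given here.

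It can also be said that multiplicity is commonly left to a statistical analysis plan, which is not shown. That carries little weight here, because the article is not silent: it fixes an unadjusted threshold for all tests, and a later plan with adjustment would contradict it. Readers could correct three prespecified P values themselves, but they cannot supply the investigators' success rule afterwards.

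On cost, it is tempting to say that power falls to 96% at worst. The protocol does not support that: it enrols 200 to allow for refusal and loss and lists postpartum exclusions. It also counts lost participants as having stopped breastfeeding, so losses may shrink the observed difference even where they do not shrink the number analysed.

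**Conclusion.** The concern holds in conditional form. The protocol has three unranked primary time points, an unadjusted 5% threshold for each and no success rule. If any one month suffices, the false-positive rate is about 8 to 14% two-sided, and about 4 to 7% in the intervention's favour against 2.5%. The upper ends (14.3% and 7.3%) assume independence. The lower ends (8.4% and 4.2%) assume a correlation of 0.9 between all visits. The documents supply nothing that would narrow the range. If all three months are required, the error is controlled but the power claim for 93 per arm is not secured. Either way the rule has to be stated, because it determines what the trial's main result means and cannot be credibly chosen once results are known.

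**What to change.** Before any outcome data are seen, do one of the following:

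- Name one month as the single primary time point, tested at two-sided 5%, and make the other two secondary. This costs no power.
- Keep all three months under Holm's procedure at overall two-sided 5%. State that success is claimed only for the months that survive it, and say outright whether one surviving month is enough to call the trial positive.

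Then amend the closing significance sentence in Data management and analysis so that it no longer gives every primary test its own 5%. In Sample size calculation, limit the claim for 93 per arm to a single test at 5%.

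The Holm option has a price. At its strictest step, for 29.2% v 49.2%, power falls from 98.5% to 95.9% with 200 evaluable per arm and from 95.9% to 90.3% with 160. It is 65.8% at 93, and 124 evaluable per arm are needed for 80%. These figures apply the planned difference to a single month, with no dilution from losses. The planned enrolment of 200 per arm leaves room for this as long as at least 124 per arm remain evaluable. No visit, procedure or recruitment target needs to change.
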